## Abstract

**Background:**

Mental health problems are common among people with diabetes. However, evidence-based strategies for the prevention and early intervention of emotional problems in people with diabetes are lacking. Our aim is to assess the real-world effectiveness, cost-effectiveness, and implementation of a Low-Intensity mental health Support via a Telehealth Enabled Network (LISTEN), facilitated by diabetes health professionals (HPs).

**Methods:**

A hybrid type I effectiveness-implementation trial, including a two-arm parallel randomised controlled trial, alongside mixed methods process evaluation. Recruited primarily via the National Diabetes Services Scheme, Australian adults with diabetes (*N* = 454) will be eligible if they are experiencing elevated diabetes distress. Participants are randomised (1:1 ratio) to LISTEN—a brief, low-intensity mental health support program based on a problem-solving therapy framework and delivered via telehealth (intervention) or usual care (web-based resources about diabetes and emotional health). Data are collected via online assessments at baseline (T0), 8 weeks (T1) and 6 months (T2, primary endpoint) follow-up. The primary outcome is between-group differences in diabetes distress at T2. Secondary outcomes include the immediate (T1) and longer-term (T2) effect of the intervention on psychological distress, general emotional well-being, and coping self-efficacy. A within-trial economic evaluation will be conducted. Implementation outcomes will be assessed using mixed methods, according to the Reach, Effectiveness, Adoption, Implementation, and Maintenance (RE-AIM) framework. Data collection will include qualitative interviews and field notes.

**Discussion:**

It is anticipated that LISTEN will reduce diabetes distress among adults with diabetes. The pragmatic trial results will determine whether LISTEN is effective, cost-effective, and should be implemented at scale. Qualitative findings will be used to refine the intervention and implementation strategies as required.

**Trial registration:**

This trial has been registered with the Australian New Zealand Clinical Trials Registry (ACTRN: ACTRN12622000168752) on 1 February, 2022.

**Supplementary Information:**

The online version contains supplementary material available at 10.1186/s13063-023-07338-5.

## Background

Around 50% of adults with diabetes experience mental health problems [1, 2], including depression, anxiety and diabetes distress (i.e. the negative emotional or affective experience resulting from the challenge of living with the demands of diabetes) [3]. There is increasing recognition of the impact of living with diabetes on emotional and mental health, and that this needs to be addressed as part of comprehensive diabetes care [4, 5]. Mental health problems are a major obstacle to effective diabetes self-management [6] and persistent diabetes distress can be a precursor to depression [7]. Both are associated with sub-optimal glycated haemoglobin (HbA1c: an important indicator of risk for macrovascular and microvascular complications) [8], reduced quality of life, work absenteeism, and increased healthcare costs [9–12]. Early intervention, using evidence-based approaches, may prevent the escalation of symptoms to severe psychological distress, enhance self-management behaviours and improve quality of life, health outcomes [13].

Importantly, people with diabetes want to discuss their emotional well-being with diabetes health professionals (HPs) [14], and they value their diabetes HPs showing empathy and acknowledging the emotional challenges faced in self-managing their condition [15]. However, data from a multi-national survey (17 countries) of diabetes health professionals showed that such discussions tend to be limited [16]. HPs report a lack of training, skills, confidence, time and other resources to attend to the emotional needs of people with diabetes [6], and would like further training and support [16, 17].

There is encouraging evidence for the effectiveness of diabetes-tailored psychological interventions for reducing diabetes distress [18]. However, such interventions are rarely implemented by HPs in clinical practice due to the aforementioned barriers, including a lack of training and skills. Diabetes HPs may be well-placed to deliver low-intensity mental health interventions, which are brief, and aim to provide a less costly approach than ‘standard’ psychological therapy [19]. Such interventions focus on supporting self-management and skills development, typically do not require delivery by a mental health professional, and provide a key service platform within a mental health stepped care model [19]. Brief problem-solving therapy (PST) is an evidence-based, low-intensity psychological intervention in which the person is supported by a health professional to learn and apply problem-solving strategies in a structured way. Brief PST is typically delivered over 4–6 sessions and is suitable for delivery by a broad range of health professionals in various settings, including telephone, with high fidelity [20–23]. Pilot data suggests brief PST reduces diabetes distress and subthreshold depressive symptoms among adults with diabetes-related retinopathy [24].

The aim of the LISTEN (*L*ow-*I*ntensity mental health *S*upport via *T*elehealth *E*nabled *N*etwork) program is to provide evidence-based, early intervention to support adults with type 1 and type 2 diabetes experiencing diabetes distress. LISTEN will be facilitated by diabetes HPs (including credentialled diabetes educators, nurses, and dietitians) who will participate in an evidence-based training program. LISTEN uses brief PST as a framework for enhancing problem-solving skills, one of seven core diabetes self-management behaviours [25]. We have demonstrated the feasibility and acceptability of training diabetes health professionals to facilitate LISTEN, and of delivering such a program to adults with diabetes [23]. Our research has also suggested potential benefits of the approach, which need confirmation in a fully powered trial.

Our aims are threefold: (1) to examine the effectiveness and (2) cost-effectiveness of LISTEN for reducing diabetes distress and improving general emotional well-being among adults with type 1 and type 2 diabetes, in a hybrid type I effectiveness-implementation trial. The third aim is to explore the barriers to, and facilitators of, the adoption, implementation and sustainability of LISTEN when facilitated by diabetes HPs via telehealth. We hypothesise that LISTEN will (1) decrease levels of diabetes distress significantly at 6 months, compared to usual care; and (2) be cost-effective, with an incremental cost-effectiveness ratio below the commonly used threshold of $50,000/quality-adjusted life year (QALY).

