#### Consent and procedure

The schedule of enrolment, intervention and assessment is detailed in Fig. 1. Study recruitment will be open for a maximum of 8 months (Fig. 2) or until the sample size (enrolled) is reached. Participation (from study entry to exit) will be for a duration of 6 months.

People with diabetes who are interested in participating will be directed to the study website to access the Plain Language Statement and provide informed consent. After providing consent, they will complete screening questions. Eligibility will be determined automatically based on responses. Those eligible will complete an online baseline assessment (T0) (hosted by Qualtrics™) and, will be randomly allocated to one of two study arms. Those who are ineligible will be informed immediately using an autogenerated message and provided with links to resources for mental health support.

Participants will be sent an email and SMS invitation with a link to the online follow-up assessment at 8 weeks (T1) and 6 months (T2) post-randomisation and allocation to the intervention or comparison group. The 8-week survey will be available for completion for 2 weeks. At the end of the first week, an email and SMS reminder will be sent to those who have not completed the survey. The 6-month survey will be available for completion for 3 weeks, with two reminders sent to non-responders at one and 2 weeks.

Participants will be e-mailed a $30 voucher on completion of the study (i.e. complete baseline, 8-week and 6-month follow-up assessments) as a token of appreciation, and to aid recruitment and retention.

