#### Secondary outcomes

General psychological distress will be assessed using the Kessler Psychological Distress Scale (K10). The scale contains 10 items about emotional states, rated on a five‐point scale, ranging from ‘*none of the time*’ to ‘*all of the time*’. The K10 score ranges from 10 to 50, with a higher score indicating greater psychological distress [33].

General emotional well-being will be assessed using the World Health Organization 5-item Well-being Index (WHO-5) [34]. Participants indicate symptom frequency over the past 2 weeks (0 = ‘*at no time*’ to 5 = ‘*all of the time*’). Item scores are summed and standardised to form a total score from 0 to 100. Higher scores represent better general emotional well-being.

Perceived ability to cope effectively with life challenges will be assessed using the Coping Self-Efficacy Scale (CSES) [35], which includes 26 items, each rated on a 11-point Likert scale, ranging from 0 (‘*cannot do at all*’) to 10 (‘*certain can do*’). Items form three subscales: problem-focused coping (12 items), stopping unpleasant emotions and thoughts (9 items) and getting support from family and friends (5 items), with higher scores indicating greater CSE. The total CSES scale score ranges from 0 to 260.

Generic health-related quality of life will be assessed using the 12-item Four-Dimensional Assessment of Quality-of-Life Instrument (AQoL4D) [36]. The scoring algorithm provides a total utility score on a scale from 0 to 1, based on Australian preferences for specific health states represented within the response items.

Information about the use of mental healthcare resources and lost productivity due to mental health problems will be captured using a Mental Health Resource Use and Productivity Impacts Questionnaire [37, 38].

The intervention group will also be invited to complete the Goal Attainment Scale [39]. At the beginning of their first LISTEN session, participants will set a goal for what they would like to achieve from the sessions. This will be recorded by the participant (or facilitating HP) on the PST worksheet. At the conclusion of their final session, participants will rate the extent to which their individual goals are attained (− 2 ‘*much less than expected*’ to + 2 ‘*much more than expected*’).

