### Economic evaluation

To assess, from a health sector and broader societal perspective, the value for money of LISTEN compared to usual care (comparison), a within-trial economic evaluation will be undertaken along with economic modelling.

Detailed costing of the LISTEN intervention will be undertaken using financial data and micro-costing methods. At each time point within the trial, participants will be asked to complete a brief resource use questionnaire to collect information about other healthcare resources used and lost productivity [37, 38]. Participants will also be asked for consent to access their Medicare Benefit Schedule (MBS) and Pharmaceutical Benefits Scheme (PBS) data containing administrative information (numbers and cost details) on visits to health care providers and prescription medication covering the same time frame of study participation.

The AQoL-4D utility values for each participant at each time point will be used to calculate QALYs [45] using the area under the curve method. The within-trial economic evaluation will measure and value any change in healthcare resource use and then compare any additional costs to additional QALYs through an incremental cost-effectiveness ratio (ICER). Bootstrapping will be used to determine confidence intervals for the ICER and construct an acceptability curve to determine the cost-effectiveness of the intervention against the commonly used willingness-to-pay threshold of $50,000/QALY [46]. Sensitivity analyses will be undertaken to evaluate the robustness of results with changes to costing or analytical assumptions.

Scale-up and implementation costs as well as longer-term cost-effectiveness will be estimated based on population-wide modelling techniques based on published epidemiological data.

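### The cost-effectiveness hypothesis (ICER below $50,000/QALY) sets no condition on the sign of the QALY difference, and the planned bootstrap interval for the ICER loses its meaning if replicates cross zero QALYs

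*Protocol article*

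**What the plan says.** The Background section ends with two hypotheses. The second is that LISTEN will "be cost-effective, with an incremental cost-effectiveness ratio below the commonly used threshold of $50,000/quality-adjusted life year (QALY". It states no condition on the sign of the cost difference or of the QALY difference.

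The Economic evaluation section gives the method. AQoL-4D utilities "will be used to calculate QALYs [45] using the area under the curve method", and the evaluation will "compare any additional costs to additional QALYs through an incremental cost-effectiveness ratio (ICER". On uncertainty it says: "Bootstrapping will be used to determine confidence intervals for the ICER". The same sentence goes on to "construct an acceptability curve to determine the cost-effectiveness of the intervention" at the same $50,000/QALY threshold. The section does not mention net monetary benefit or the handling of negative ratios.

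Two other facts bear on the size of the QALY difference. Utility is a "total utility score on a scale from 0 to 1" (Secondary outcomes), and "Participation (from study entry to exit) will be for a duration of 6 months" (Consent and procedure).

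**The concern.** A ratio below a threshold means good value only when the denominator is positive. If LISTEN costs more and loses QALYs, the ICER is negative and lies below $50,000. If it saves money and loses QALYs, the inequality reverses: an ICER below $50,000 then means that too little is saved for the health given up.

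The interval inherits the same problem. The ratio is discontinuous where the QALY difference is zero. If bootstrap replicates fall on both sides, ranking them by ICER places dominant results (cheaper, better) beside dominated ones (dearer, worse), and the limits of the interval no longer bracket worse to better value.

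Cost-effectiveness is one of the two stated hypotheses, and the abstract says that the results will inform whether LISTEN should be implemented at scale. The criterion should therefore classify every possible result correctly.

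**Working it through.** **Inputs from the article.** Threshold $50,000/QALY; utility range 0 to 1; 6 months of participation; 113 per arm as the minimum analysable sample (Sample size). The article gives no expected cost difference, QALY difference, SD or ICER, so there is no economic figure to reproduce.

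**Step 1: the criterion, with no assumption about the trial's results.** Let dC be the cost difference and dQ the QALY difference (LISTEN minus usual care). ICER = dC/dQ. Net monetary benefit NMB = 50,000 × dQ − dC, and LISTEN is cost-effective at the threshold when NMB > 0. Illustrative pairs:

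| dC | dQ | ICER | Below $50,000? | NMB | Cost-effective? |
|---|---|---|---|---|---|
| +$500 | +0.02 | $25,000 | yes | +$500 | yes |
| −$500 | +0.005 | −$100,000 | yes | +$750 | yes |
| +$500 | −0.005 | −$100,000 | yes | −$750 | **no** |
| −$100 | −0.02 | $5,000 | yes | −$900 | **no** |
| −$1,500 | −0.02 | $75,000 | no | +$500 | **yes** |

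Rows two and three have the same ICER and opposite meanings. Rows three to five are misclassified by the ICER wording; all have dQ < 0. When dQ > 0 the two criteria agree.

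**Step 2: is a QALY difference near zero plausible?** The most one person can accrue is 1 × 0.5 year = 0.5 QALY. A constant utility gain of 0.02 held for the whole period gives 0.02 × 0.5 = 0.01 QALY, worth 50,000 × 0.01 = $500 at the threshold. A small difference is therefore plausible, but the article does not fix it.

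**Step 3: size, under assumed inputs.** Assume dC averages $300 with SE 300, and dQ has SE 0.008, both normal and independent. At 113 per arm these SEs correspond to SDs of 0.008/√(2/113) ≈ 0.06 QALY and 300/√(2/113) ≈ $2,255.

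The SE of NMB is √((50,000 × 0.008)² + 300²) = √(400² + 300²) = $500. So P(NMB > 0) = Φ((50,000 × dQ − 300)/500):
- dQ = 0: Φ(−0.6) = 0.27
- dQ = +0.005: Φ(−0.1) = 0.46
- dQ = +0.01: Φ(0.4) = 0.66
- dQ = +0.02: Φ(1.4) = 0.92

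P(ICER < 50,000) adds two regions: dQ > 0 with NMB > 0, and dQ < 0 with NMB < 0. Only the first is cost-effective. The last column is the 2.5th to 97.5th percentile of simulated ICERs.

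| True dQ | P(ICER < 50,000) | P(NMB > 0) | Central 95% of ICERs, about |
|---|---|---|---|
| 0 | 0.73 | 0.27 | −$0.70m to +$0.70m |
| +0.005 | 0.70 | 0.46 | −$0.55m to +$0.59m |
| +0.01 | 0.75 | 0.66 | −$0.28m to +$0.35m |
| +0.02 | 0.92 | 0.92 | −$19,000 to +$85,000 |

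At dQ = 0, half of the draws have a QALY loss, and 0.5 × Φ(1) = 42% of all draws are dominated.

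**Step 4: sensitivity to the assumptions.** With mean dC $500, cost SD $2,000 and 113 per arm, the shares P(ICER < 50,000) v P(NMB > 0) are:

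| True dQ | QALY SD 0.05 | QALY SD 0.10 |
|---|---|---|
| 0 | 0.62 v 0.12 | 0.74 v 0.25 |
| +0.005 | 0.50 v 0.28 | 0.72 v 0.37 |
| +0.01 | 0.56 v 0.50 | 0.73 v 0.50 |
| +0.02 | 0.88 v 0.88 | 0.83 v 0.76 |

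The pattern is the same. The gap closes as the QALY gain grows relative to its SE: it has gone at +0.02 with SD 0.05, but not yet with SD 0.10.

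**The case against.** The strongest reply is that the protocol already plans the right tool. The sentence on bootstrapping assigns to the acceptability curve the task of judging cost-effectiveness at $50,000/QALY. Built in the standard way, that curve is the share of replicates with positive net benefit: it counts dominated replicates as not cost-effective and stays interpretable when the QALY difference is near zero. This stands. The article does not say how the curve will be built, but nothing in it suggests a wrong construction.

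Second, the ICER statement is a hypothesis in the Background, not a formal decision rule, and the economic section's wording of additional costs against additional QALYs suggests that the authors had the usual quadrant in mind. A reader might infer that the trial would declare a dearer, worse LISTEN cost-effective; the document does not support that. What stands against this defence is narrower: the usual quadrant is implied and not required, so the literal hypothesis and the curve can disagree.

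Third, the interval problem is conditional. A reader might infer that replicates are bound to straddle zero QALYs. The article gives no expected difference or SD, and with the larger gains shown above the problem all but disappears. Nor does it say that a percentile method will be used. That matters little, because the difficulty lies in ordering ratios across a sign change in the denominator.

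Fourth, quadrant handling might be left to a fuller analysis plan. That would excuse silence, but here the article itself names the criterion and the quantity that gets the interval.

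**Conclusion.** The point holds in a limited form. The hypothesis as worded is met by any dominated result and can misclassify a cheaper but worse one; this is algebra and needs no assumption about the trial's results. The planned confidence interval for the ICER would be uninterpretable if replicates cross zero on the QALY axis. Whether they will is unknown. Under the first set of assumed inputs, the ICER wording overstates the share of favourable replicates by 46 percentage points at a QALY difference of 0, by 24 at +0.005, by 9 at +0.01, and by essentially none at +0.02. These figures rest on assumed costs, SEs, normality and independence, none of which the article supplies.

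The planned acceptability curve, built from net benefit, is not at fault, and the primary clinical outcome is untouched. Severity is minor to moderate.

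**What to change.** - Restate the second hypothesis as: incremental net monetary benefit at $50,000/QALY is greater than zero.
- Replace the confidence interval for the ICER with a bootstrap 95% confidence interval for incremental net monetary benefit.
- Keep the acceptability curve, and state that it plots the share of replicates with positive net benefit at each threshold.
- Report the ICER as a point estimate, with the share of replicates in each quadrant of the cost-effectiveness plane.

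The cost is a few sentences in the hypothesis and the economic evaluation. The data and the bootstrap replicates are the same, and nothing changes for participants or for the primary analysis.

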## Methods

### Design

This study uses a hybrid type I effectiveness-implementation trial design [26] to test the effectiveness of LISTEN in a two-arm pragmatic, individual-level randomised controlled trial (RCT). We will simultaneously gather information on any barriers to, and facilitators of, implementation [26]. LISTEN (intervention) will be compared to usual care (comparison group), in terms of its impact on diabetes distress at 8 weeks (T1) and 6 months (T2) post-randomisation. To assess the cost-effectiveness of LISTEN, a within-trial economic evaluation will be conducted. Implementation will be examined using mixed-methods, and in accordance with the RE-AIM (Reach, Effectiveness, Adoption, Implementation and Maintenance) framework [27]. The Consolidated Framework for Implementation Research (CFIR) will inform exploration of multi-level barriers to, and facilitators of implementation and sustainability — including identification of implementation strategies to maximise delivery.

The protocol has been prepared according to the Standard Protocol Items: Recommendations for Intervention Trials (SPIRIT) statement. See Fig. 1 for schedule of enrolment, interventions, and assessments, as per the SPIRIT statement. Figure 2 shows the study flow. The trial will be reported in accordance with CONSORT guidelines for RCTs. The project board will meet quarterly to monitor the project timeline, risks, and quality assurance processes.

**Fig. 1 Fig1:**
[figure not shown]
LISTEN trial schedule of enrolment, interventions, and assessments. HP, health professional; T0, baseline, T1, 8 weeks post-randomisation and allocation; T2, 6 months post-randomisation and allocation; PAID, Problem Areas in Diabetes Scale; PHQ-4, Patient Health Questionnaire-4; K10, Kessler Psychological Distress Scale; WHO-5, The World Health Organization-Five Well-Being Index; CSE, Coping Self Efficacy Scale; AQoL-4D, The Assessment of Quality of Life four-dimension instrument; MBS, Medicare Benefit Schedule, PBS, Pharmaceutical Benefits Scheme data

**Fig. 2 Fig2:**
[figure not shown]
Flow of participants in the LISTEN study. HP, health professional; CFIR, Consolidated Framework for Implementation Research; NDSS, National Diabetes Services Scheme; PAID, Problem Areas in Diabetes Scale; PHQ-4, Patient Health Questionnaire-4; K10, Kessler Psychological Distress Scale; WHO-5, The World Health Organization-Five Well-Being Index; CSE, Coping Self Efficacy Scale; AQoL-4D, The Assessment of Quality of Life four-dimension instrument; TFA, Theoretical Framework of Acceptability

### Effectiveness trial

#### Participants and recruitment

Potential participants will be enrolled if they meet the inclusion criteria: adult aged 18 to 75 years; residing in Australia; self-reported diagnosis of type 1 or type 2 diabetes; at least mild diabetes distress (score ≥ 25 on the Problem Areas in Diabetes (PAID) scale (or a score of ≥ 2 (moderate problem) on three or more PAID items). LISTEN aims to provide early intervention to participants experiencing mild symptoms of depression and/or anxiety. Therefore, those with moderate-to-severe depression and/or anxiety symptoms (as indicated by a score ≥ 3 on either the depression or anxiety subscales of the four-item Patient Health Questionnaire (PHQ-4) will be excluded. Those with a score ≥ 3 will be referred to appropriate mental health services. A summary of the mental health inclusion criteria and referral pathways is in Supplementary File 1.

Participant recruitment will be primarily via e-mail invitation to adults with diabetes registered with the National Diabetes Services Scheme (NDSS). The NDSS is an Australian Government initiative, administered by Diabetes Australia, providing access to services, information and subsidised diabetes products (e.g. glucose monitoring supplies and insulin pump consumables). The NDSS register includes over 1.4 million Australians with diabetes and is considered reasonably accurate and up-to-date [28]. The NDSS will email invitations directly to potential participants on behalf of the project team. The research team will not have access to personal details unless potential participants make contact, or enrol in the study. E-mail invitations will be staggered over a 6–8-month recruitment period.

In addition, the study will be advertised on the Australian Centre for Behavioural Research in Diabetes (ACBRD) website, e-newsletter/blogs and social media (Twitter, Facebook) via the researchers’ affiliated professional accounts (e.g. Deakin University, ACBRD). National and state-based diabetes organisations (e.g. Diabetes Australia and Diabetes Victoria) will be encouraged to promote the study through similar methods.

